#### *1.1.3 Treatments of sepsis*

The mainstay of sepsis treatment in the initial phase includes intravenous (IV) antibiotics and fluids, source control, and supportive care, if necessary.

The international Surviving Sepsis Campaign (SSC), which is supported by 25 medical societies, guides in treatment of septic shock, but does not give any recommendations on sepsis patients not in overt shock in general, despite the fact that sepsis is almost 60 times as common as septic shock. The 1-hour bundle, introduced by SSC, recommends initiation of sepsis-treatment including fluids for hypotension/lactate  $> 4\text{mmol/L}$  within 1 hour. In general, many sepsis studies have been conducted – especially in septic shock – but only very few have been proved effective leaving the clinician with only few evidence-based interventions for treatment.

## **1.2 Fluid – the trial intervention**

### *1.2.1 Use of fluids*

Intravenous fluid therapy is one of the most common therapeutic interventions performed in the ED. The most frequently used fluid, normal saline (0.9% NaCl), was described more than 100 years ago and the use was introduced to cholera patients. Other crystalloids and colloids have been introduced, especially with the intention to balance solutions by electrolyte composition and osmolality to approximate to human plasma.

IV fluids for patients are used for different reasons; resuscitation (i.e., mostly to raise blood pressure and tissue perfusion), replacement of loss (e.g., vomit, diarrhea, perspiration, dehydration), maintenance to cover daily needs, correction of electrolytes, and as adjuvant for medications given intravenously.

The goals of fluids administration in terms of resuscitation is to increase intravascular volume. The increased intravascular volume is intended to improve cardiac output and tissue oxygenation/perfusion. The requirements for and response to fluid resuscitation vary greatly during the course of any critical illness. No single physiological or biochemical measurement adequately reflects the complexity of fluid depletion nor the response to fluid resuscitation in acute illness.

Although the physiology of fluid treatment is not fully understood and elucidated, it probably should be regarded as a kind of medication with both intended effects and adverse reactions. However, evidence to decide on this is sparse; “What is the optimal fluid treatment?” remains an unanswered question.

### *1.2.3 Fluid restriction; pros and cons*

Recent fluid resuscitation and use seems to be quite liberal, in accordance with SSC, used for the above-mentioned reasons (section 1.2.1). However, too liberal fluid resuscitation may potentially result in worsening of tissue edema (including lungs), challenge the heart and lengthen the duration of mechanical ventilation. Liberal fluid resuscitation may also result in increased hemodilution, which may induce use of concomitant interventions (e.g., transfusion of blood products). Intravenous fluid administration has also been suggested to cause destruction of the capillary wall, causing further tissue edema. Restrictive fluid therapy may be beneficial in reducing venous backpressure and organ edema, thereby improving function of organs such as the lungs, gut, and kidneys. On the other hand, fluid restriction may compromise peripheral and/or organ perfusion through reduced cardiac output and thereby reduced microcirculation from the arterial side.

#### 1.2.4 Use in sepsis

Fluid resuscitation has, as mentioned, been a corner stone of sepsis treatment for years. Liberal fluid therapy for septic patients has been recommended since the first Surviving Sepsis Campaign guideline (SSC, 2003). The SSC's 2016-guidelines recommend at least 30 mL/kg of IV crystalloid fluid to be given within the first 3 hours (strong recommendation, low quality of evidence) for patients in septic shock.

However, as seen, fluid resuscitation is guided by low quality of evidence and studies show great variation in practice. A yet unpublished study performed in our research group showed a great variability in fluids for sepsis patients with a range from 200-15870 ml. Patients with sepsis received approximately 3762 ml (standard deviation: 1839) fluids in total for 24 hours and patients with sepsis, blood cultures drawn and intravenous antibiotics received 2670 ml intravenous fluids (SD 1695). The physiology of fluid resuscitation in sepsis is not fully understood but fluid overload has been suggested to be harmful in multiple studies. Multiple studies have, reproducibly, demonstrated that only approximately 50% of hemodynamically unstable patients will respond to a fluid challenge – so called fluid responders. And it is unclear if the fluid responders obtain benefits from fluid beyond those observed as short-term hemodynamic effects.

### 1.3 Trials in fluid and sepsis

Within the last decade, there has been an increase in observational studies and interventional trials on fluid and septic shock with a number of randomized trials ongoing.

A systematic review of predominantly observational studies found that positive fluid balance was associated with increased mortality. A recent review and meta-analysis of randomized trials found no statistically significant difference between lower vs. higher fluid volumes in all-cause mortality. The study only included five trials and found low quality of evidence supporting the decision on the volumes of IV fluid therapy in adults with septic shock and sepsis. All five trials were in the intensive care units (ICU) setting.

A recent randomized pilot trial by Hjortrup et al. (included in the above mentioned review) was able to reduce volumes of resuscitation fluids with a restrictive fluid protocol in septic shock patients in the ICU. Another pilot trial in the ED by Macdonald et al. was able to reduce fluids with 30% with a fluid restrictive and early vasopressor approach in patients with sepsis associated hypotension. The patient-centered outcomes in the study by Hjortrup et al. pointed towards benefit with fluid restriction with no negative effects on hemodynamic measurements. However, the trial was underpowered to show differences in clinical outcomes. Both studies are now enrolling patients in large-scale randomized trials; the CLASSIC-trial (ClinicalTrials.gov Identifier: NCT03668236) enrolling ICU patients in Europe and the REFRESH-

trial/ARISE-FLUIDS (ClinicalTrials.gov Identifier: NCT04569942) enrolling ED patients in Australia and New Zealand. Another randomized trial, CLOVERS (ClinicalTrials.gov Identifier: NCT03434028), is enrolling persistent hypotensive patients in EDs in United States to either liberal or restrictive fluids for 24 hours.

Although trials are currently exploring fluid strategies in patients with hypotension and septic shock, there are no studies on fluid administration in patients with early sepsis without shock/hypotension. Research within this field has been requested by experts. As fluid administration is very frequent, but not evidence-based, and carries potential risks, we consider it to be of great interest for society and patients to perform research in this area. Fluid resuscitation is a key intervention in sepsis, but the optimal amount of fluid to be given has not been established. The present trial is a feasibility trial, i.e., a trial assessing the feasibility of the proposed protocol in a clinical setting. The aim is to investigate the ability to reduce fluid volume using the given protocol. Should the trial prove feasible with separation between the two interventions, a large-scale trial assessing patient important outcomes is intended.

## 2. TRIAL OBJECTIVES AND HYPOTHESES

Primary objective: To test if an IV fluid restrictive protocol in ED patients with sepsis is feasible, i.e., if the protocol decreases the IV fluid volumes administered.

Hypothesis: An IV fluid restrictive protocol is feasible in sepsis patients resulting in significantly less IV fluid volume administration as compared with standard care.

### 3. TRIAL DESIGN

#### 3.1 Overview

This is an investigator-initiated, multicenter, randomized, parallel-group, open-labeled, feasibility trial investigating volumes of fluid within 24 hours in 124 patients with sepsis allocated to two different IV fluid regimens enrolled at three emergency departments in Central Region Denmark. The objective is to assess the feasibility of a trial comparing two approaches to intravenous fluid resuscitation of sepsis; a restrictive approach using four criteria vs. standard care. The hypothesis is that the restrictive approach is feasible and will result in less IV fluid given. The primary outcome is total intravenous fluid volume within 24 hours and key secondary outcomes include protocol violations, total fluids (intravenous and oral) within 24 hours, progression to septic shock, and SAEs/SUSARs.

#### 3.2 Allocation

Patients fulfilling all inclusion criteria and no exclusion criteria will be randomized in a 1:1 ratio in blocks of varying concealed sizes stratified by site at enrollment to one of two fluid treatment arms lasting for the first 24 hours of admission or until the patient is discharged within 24 hours. Randomization will be performed via the web-based randomization system provided in REDCap ensuring allocation concealment.

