## **3.5 Trial procedures**

### *3.5.1 Patients*

The trial procedures will be limited to the interventions given in the first 24 hours of admission. Data will be obtained from the study specific case report form and the electronic medical records.

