### **4.2 Inclusion criteria**

The research team, clinically working nurses and ED physicians will screen ED patients for the following inclusion criteria:

- 1) Unplanned emergency department admission
- 2) Age  $\geq 18$  years
- 3) Sepsis defined as
  - a) suspected infection by the treating clinician AND
  - b) blood cultures drawn AND
  - c) IV antibiotics administered or planned AND
  - d) An infection related increase of SOFA-score  $\geq 2$  from baseline
- 4) Expected hospital stay > 24 hours as deemed by treating clinician

These broad inclusion criteria were chosen to investigate the effect of fluid administration in the entire, broad sepsis population and increase the likelihood of describing the entire 24 hours inclusion period. We will strive to enroll participants as soon as they fulfill the criteria in the ED. There is no exact maximum time frame for patient inclusion, however with the exclusion criteria of > 500 ml. IV fluids administered, the inclusion is expected and intended to happen within the first couple of hours.

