### **5. OUTCOMES**

#### **5.1 Primary outcome**

##### *5.1.1 Definition*

The primary outcome will be the total amount of all administered intravenous, crystalloid fluids within 24 hours of randomization.

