#### **5.2 Secondary outcomes**

##### *5.2.1 Definitions*

The secondary outcomes will be

- Feasibility measures:
  - Number of patients with major protocol violations,

- Number of patients screened positive (ie.with all inclusion criteria fulfilled and no exclusion criteria fulfilled) vs randomized
- Time from admission to inclusion
- Number of patients lost to follow up in terms of 24-hour fluids (e.g. due to discharge within 24 hours)
- Accumulated serious adverse reactions and events (SAEs + SARs+ SUSARs) within 7 days in-hospital
- Total fluids (oral and intravenous) at 24 hours

We will also report in-hospital mortality and 30- and 90-day mortality (possible outcomes for the final large scale trial), in-hospital length of stay (LOS), mechanical ventilation within 7 days of admission (yes/no), vasopressor use within 7 days of admission (yes/no), and development or worsening of acute kidney failure according to the KDIGO3-criteria within 7 days of admission (also an SAE, see above) .

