#### *5.4.3 Assessment of adverse events*

##### *Timing*

In all participants, we will assess the occurrence of SARs in the 7 days following randomization (the intervention period is 24 hours; 7 days allow for another 6 days of assessment after the intervention, which is clinically relevant in critically ill patients).

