#### *7.1.6 Variables obtained at 6-, 12- and 24 hours after randomization:*

Hourly volumes of resuscitation fluid with specification of indication for each fluid bolus

Other fluids including blood products, nutrition, fluid with medication

Highest creatinine within 24 hours to evaluate KDIGO-criteria

Only 24hours: To evaluate worst SOFA-score within 24 hours:

Results of blood samples (standard lab. Values + arterial/venous blood gas)

- Lowest values: platelets, PaO2 (and FiO2)
- Highest values: lactate, bilirubin,

Use of renal replacement therapy Y/N

Protocol violations

Non-invasive ventilation Y/N

On mechanical invasive ventilation or vasopressor Y/N

Status: dead, Y/N

Only 24hours: SAEs (see section 5.4.3) + SARs (see section 5.4.4)

SAEs on this day (y/n for everyone)

- Cerebral ischemic event
- Myocardial ischemic event
- Intestinal ischemic event
- Limb ischemia
- New onset of severe acute kidney injury

SARs on this day (y/n for everyone)

- General tonic-clonic seizures
- Anaphylactic reactions
- Central pontine myelinolysis
- Severe hyponatremia
- Severe hyperchloremic acidosis
- Severe metabolic alkalosis

Only 24 hours: SUSARs

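### Sections 3.2 and 3.5.1 end the fluid regimen 24 hours after admission, but the primary outcome and the violation record run to 24 hours after randomization

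*Protocol*

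**What the plan says.** Two sections fix how long the intervention lasts, and both count from admission. Section 3.2 describes "two fluid treatment arms lasting for the first 24 hours of admission or until the patient is discharged within 24 hours". Section 3.5.1 adds: "The trial procedures will be limited to the interventions given in the first 24 hours of admission".

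The measurement sections count from randomization. Section 5.1.1: "The primary outcome will be the total amount of all administered intravenous, crystalloid fluids within 24 hours of randomization". Section 7.1.6 lists hourly fluid volumes and protocol violations under the heading "Variables obtained at 6-, 12- and 24 hours after randomization". The safety timing in 5.4.3 places a 24-hour intervention inside the seven days after randomization: "the intervention period is 24 hours; 7 days allow for another 6 days of assessment after the intervention".

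On the gap between the two starting points, section 4.2 says "There is no exact maximum time frame for patient inclusion", though "the inclusion is expected and intended to happen within the first couple of hours" because of the limit on prior fluid. Section 5.2.1 makes "Time from admission to inclusion" a feasibility outcome.

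**The concern.** The two clocks cannot coincide. Before randomization a patient needs suspected infection, blood cultures, antibiotics given or planned, a SOFA rise that depends on laboratory results, and consent from a trial guardian. Every patient therefore has some delay, and under the wording of 3.2 the allocated regimen ends that much earlier than the outcome window.

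Two things are at stake.

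- **The primary contrast.** The trial exists to show that the protocol separates the arms on IV fluid. Hours that count toward the outcome but lie outside the regimen dilute the difference.
- **The violation count.** The definition of a major violation in 3.3.5 has no time limit. Restrictive-arm fluid given after 24 hours of admission but before 24 hours from randomization is outside the regimen under 3.2, is recorded under 7.1.6, and may or may not be a violation under 3.3.5. Sites could classify it differently, and major violations are the first feasibility measure listed in 5.2.1.

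Bedside staff get little help elsewhere. The chart described in 7.1 covers a 24-hour period with no stated start, and the oliguria trigger in 3.3.1 does use an admission clock.

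**Working it through.** **The texts side by side**

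| Item | Section | Clock |
|---|---|---|
| Duration of the arms | 3.2 | admission |
| Interventions and procedures | 3.5.1 | admission |
| Primary outcome | 5.1.1 | randomization |
| Fluid and violation recording | 7.1.6 | randomization |
| Safety follow-up, 24 h intervention plus 6 days | 5.4.3 | randomization |

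With a delay of h hours from admission to randomization, the regimen under 3.2 covers only 24 − h of the 24 outcome hours. The contradiction rests on this comparison alone. The arithmetic below only shows its possible size.

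**The plan's own figure**

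Inputs from 6.1 and 6.2.1: difference 1.0 L, SD 1.7 L in both arms, two-sided 5%, 90% power, two-sample t-test. The exact t-test calculation gives 61.7 per arm, rounded up to 62, so 124 in total. The stated size reproduces.

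Power with n = 62 per arm comes from the noncentral t distribution with 122 degrees of freedom and noncentrality

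δ / (SD × √(2/n)) = 1.0 / (1.7 × √(2/62)) = 1.0 / 0.3053 = 3.28,

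which gives 90.1%. This is also the result if the regimen runs from randomization.

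**Illustration of the literal reading**

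Assumptions, none of which the protocol supplies: every patient has the same delay h, 3.2 is followed to the letter, separation stops completely when the regimen ends, and the SD does not change. Let r be the fluid rate in the last h hours relative to the 24-hour average. Then

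δ = 1 − r × h/24 litres.

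For h = 2 (the expected couple of hours), 2/24 = 8.3% of the outcome window lies outside the regimen.

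| r | Loss | Difference | Noncentrality | Power |
|---|---|---|---|---|
| 1 (even rate) | 83 ml | 0.917 L | 3.00 | 84.6% |
| 0.5 | 42 ml | 0.958 L | 3.14 | 87.6% |
| 0.25 | 21 ml | 0.979 L | 3.21 | 88.9% |

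Because 4.2 sets no maximum delay, the same calculation at an even rate (r = 1) for other delays is:

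| h | Difference | Power |
|---|---|---|
| 1 h | 0.958 L | 87.6% |
| 3 h | 0.875 L | 81.1% |
| 4 h | 0.833 L | 77.3% |
| 6 h | 0.750 L | 68.3% |

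Fluid in sepsis may well be given mostly early, in which case the smaller losses are the more realistic ones.

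**The case against.** The strongest reply is that the rest of the protocol already shows what was meant. Section 9.3.2 has patients told that interventions end with a 24-hour period tied to enrollment, and 3.2 itself randomizes at enrollment. Sections 3.3.1 and 4.2 speak of a 24-hour inclusion period. The bedside chart in 7.1 is introduced straight after enrollment and allocation, and 7.1.6 fixes the window for recording violations. The protocol is also loose with the word admission elsewhere: 5.4.5 counts SUSARs over 7 days from admission, while 5.4.3 counts from randomization. On this view 3.2 and 3.5.1 contain a slip of wording. Harm would require sites to stop early even though their chart and log run on, and even then the loss at a 2-hour delay is at most 83 ml.

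Much of this stands. Randomization is very likely the intended clock, any bias is conditional, and its likely size is modest. But none of those passages states a start time that overrides 3.2, which is the sentence that defines how long the arms last. 3.5.1 agrees with it, and 5.2.1 shows that the protocol does treat admission and inclusion as different moments. The evidence of intent tells us which sections to correct. It does not remove the need to correct them.

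**Conclusion.** The concern holds. Sections 3.2 and 3.5.1 are wrong as written, because they end the regimen on a different clock from the outcome and the violation record. It should be fixed, but the primary result is not in jeopardy: the error works only toward a smaller observed difference, and the outcome definition and the sample size are sound.

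The size depends on conduct. If sites run the regimen from randomization, the loss is zero. If they follow 3.2 literally, the illustrative loss at a 2-hour delay is 21 to 83 ml of the planned 1 L, and more with longer delays. These figures rest on an assumed common delay, an assumed late fluid rate and complete loss of separation once the regimen ends. The textual contradiction rests on none of these.

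A side point on the same outcome, on which this conclusion does not depend: 5.1.1 and the overview count crystalloid, whereas 3.1 and 6.1 refer to total IV fluid.

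**What to change.** - **Section 3.2:** state that the arms last *24 hours from randomization, or until discharge if earlier*.
- **Section 3.5.1:** replace the admission-based period with *the 24 hours from randomization*.
- **Leave unchanged:** 5.1.1, 7.1.6 and the sample size of 124.
- **Minor:** keep the crystalloid definition in 5.1.1 and use it in 3.1. A note in 6.1 that the planning figures are for total IV fluid is optional, since that section already labels them as intravenous volumes.

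Regimen, outcome window and violation recording then share one start and one end. The cost is one phrase in each of two sections plus the small wording edits. No new data are needed, because 7.1.6 already captures fluids and violations to 24 hours after randomization.

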#### 3.3 Interventions

##### 3.3.1 Restrictive fluid administration

No IV fluids should be given unless one of the below mentioned occurs; in these cases, IV fluid may be given in measured amounts:

A fluid bolus of 250 ml (half of a 500 ml fluid bag) isotonic crystalloid may be given within 15 minutes if one of the following occurs (hypoperfusion criteria):

- Lactate concentration  $\geq 4$  mmol/l (arterial or venous blood gas/blood sample)
- Hypotension (systolic BP  $< 90$  mmHg)
- Mottling beyond edge of kneecap (i.e., Mottling score  $>2$ )
- Severe oliguria, i.e., diuresis  $< 0.1$  ml/kg/h, during the first 4 hours of admission

The effect of a fluid bolus may be assessed after 30 minutes by re-evaluation of the four hypoperfusion criteria mentioned above by the treating clinician. If one or more of the criteria are still fulfilled, a fluid bolus as defined above may be repeated. At any time, the clinician can start vasopressors if deemed necessary.

Only isotonic crystalloids are to be given as resuscitation fluid; the type of isotonic crystalloid is free of choice. Crystalloid boluses are to be given via IV drip. Intravenous fluids may be given as carrier for medication, but the volume should be reduced to the lowest possible volume for the given medication.

In case of documented overt fluid losses (e.g., vomiting, large aspirates, diarrhea, drain losses, or ascites drainage or due to dehydration) IV fluid may be given to correct for the loss.

In case the oral/enteral route for water or electrolyte solutions is contraindicated or has failed as judged by the clinical team, IV fluids may be given to:

- Correct significant electrolyte deficiencies
- Ensure a total fluid input of 1 L per 24 h (fluids with medications and nutrition count as input).

If a patient undergoes surgery during the 24 hours inclusion period, they are temporarily out of the protocol, but we will encourage continuing restrictive fluid therapy.

The cut-off value of lactate was chosen based on SSC guidelines and their one-hour bundle and data indicating that the marked increase in mortality occur at lactate values above 4 mmol/l. The mottling trigger is based on mottling score  $\geq 2$  (see figure below) as described by Ait-Oufella et al and validated in a pre-hospital setting. Severe oliguria is defined as urine output  $\leq 0.1$  ml/kg/hour and the criteria is only to be used within the first 4 hours of admission.

[figure not shown]

Figure showing Mottling score, copy with permission from Ait-Oufella et al.

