### *3.3.5 Criteria for modification of interventions for a given trial participant and protocol violations*

The clinical team may at any time violate the protocol if they find it to be in the interest of the participant. We will have a 24-hour per day trial hotline to enable discussion between the clinicians caring for trial participants and the REFACED Sepsis trial team regarding protocol related issues.

Protocol violations are defined as follows:

| Intervention group               | Major protocol violation                                                                                                                                                                                                                                                                                                                                                        | Documentation                      |
|----------------------------------|---------------------------------------------------------------------------------------------------------------------------------------------------------------------------------------------------------------------------------------------------------------------------------------------------------------------------------------------------------------------------------|------------------------------------|
| Restrictive fluid administration | IV fluids given if none of the bellow is true: 

• 1 or more hypoperfusion criteria fulfilled

• To correct documented fluid loss

• To correct significant electrolyte deficiencies

• Fluid administered as carrier for medication (e.g. antibiotics)

• Ensure a total fluid input of 1 L per 24 h

 | Reasons for the protocol violation |
| Standard care                    | No IV fluids given                                                                                                                                                                                                                                                                                                                                                              | Reasons for the protocol violation |

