### *3.3.5 Assessment of participant compliance*

We will monitor protocol compliance at the trial site through the electronic case report form (eCRF) in REDCap and alert sites in the case of clear violation (central monitoring). In addition, the trial will be monitored according to the Good Clinical Practice (GCP) directive and a monitoring plan conducted in collaboration with the GCP-unit at Aarhus and Aalborg Universities.

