#### *7.1.5 Variables obtained at randomization (the closest measured around time for randomization):*

Values for SOFA-score at admission 

Results of blood samples (standard lab. Values + arterial/venous blood gas)

- Lowest values: haemoglobin, platelets, eGFR,
- Highest values: lactate, kreatinin, bilirubin, C-reactive protein, leukocytes (white blood count),

Vital parameters

- Highest heart rate, respiratory rate,
- Lowest values of mean arterial blood pressure
- Highest values of arterial or venous lactate concentration or from a blood sample

Antibiotics: Type, timing and dosage and administration form

Volume of resuscitation fluids (crystalloids, colloids and blood products in ml) until randomization

Other fluids including blood products, nutrition, fluid with medication

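### The mottling trigger for a restrictive-arm bolus has two different cut-offs in section 3.3.1, so the count of major protocol violations is not uniquely defined

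*Protocol*

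**What the plan says.** Section 3.3.1 allows a 250 ml bolus in the restrictive arm when at least one of four hypoperfusion criteria is met, and allows a repeat if a criterion is still met at re-evaluation after 30 minutes. Two of the four criteria are stated twice in that section.

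- Mottling. List: "Mottling beyond edge of kneecap (i.e., Mottling score $>2". Rationale paragraph: "The mottling trigger is based on mottling score $\geq 2$ (see figure below".
- Oliguria. List: "Severe oliguria, i.e., diuresis $< 0.1$ ml/kg/h, during the first 4 hours of admission". Rationale paragraph: "Severe oliguria is defined as urine output $\leq 0.1$ ml/kg/hour".

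The hypotension criterion, "Hypotension (systolic BP $< 90$ mmHg", and the lactate criterion each have one cut-off.

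The violation table in section 3.3.5 makes restrictive-arm IV fluid a major violation if none of five reasons holds. One of the five is "1 or more hypoperfusion criteria fulfilled". Section 5.2.1 counts patients with major violations as the first feasibility measure, and section 3.1 names protocol violations among the key secondary outcomes.

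On checking adherence, the section on participant compliance (also numbered 3.3.5) says: "We will monitor protocol compliance at the trial site through the electronic case report form (eCRF) in REDCap".

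**The concern.** The same trigger does two jobs: it tells the clinician whether a bolus is permitted, and it decides afterwards whether the bolus was a violation. If the cut-off depends on which paragraph is read, neither question has a single answer for a patient at the boundary. Three sites train their staff on these criteria and could in good faith teach different rules.

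The trial exists to judge whether this fluid protocol can be delivered before a large trial is started. Adherence is a main part of that judgement, so the definition behind the adherence count should be fixed before data are collected.

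A second, smaller question is whether the count can be checked later. The decision is made open-label by the treating team, and what the protocol lists for each bolus is the team's stated indication, not the measurement behind it.

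**Working it through.** **Step 1. The triggers side by side (all in section 3.3.1).**

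| Trigger | List | Rationale paragraph | Where they disagree |
|---|---|---|---|
| Lactate | ≥ 4 mmol/l | trigger not restated | – |
| Systolic pressure | < 90 mmHg | not restated | – |
| Mottling score | > 2 | ≥ 2 | score exactly 2 |
| Urine output | < 0.1 ml/kg/h | ≤ 0.1 ml/kg/h | exactly 0.1 |

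If the mottling score is recorded in whole steps, as both wordings suggest (the scoring figure is not in the text at hand), the disagreement covers a whole grade. For urine output, a continuous quantity, it covers a single point and has almost no practical effect.

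**Step 2. Classifying one bolus.** Take a restrictive-arm bolus given for mottling score 2, no other hypoperfusion criterion met, and none of the other four reasons in the violation table present (documented fluid loss, significant electrolyte deficiency, carrier for medication, securing 1 L of total input per 24 h).

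- By the list: 2 > 2 is false, no reason holds, so it is a major violation.
- By the rationale: 2 ≥ 2 is true, a reason holds, so it is permitted.

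**Step 3. Effect on the outcome.** Let k be the number of restrictive-arm patients with at least one such bolus and no other violation, and V the number in that arm who are violators under either reading. The count is V + k by the list and V by the rationale. With 62 patients planned in the arm, the proportion shifts by k/62, which is 1/62 = 1.6 percentage points per patient. The outcome counts patients, so repeat boluses in the same patient add 250 ml each to the volume but nothing more to the count. The protocol gives no frequency for mottling score 2, so k cannot be estimated.

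**Step 4. What is listed for checking (sections 7.1 and 7.1.3 to 7.1.9).**

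- Per bolus: timing, type, volume, indication and time to re-evaluation; also violations and their reasons.
- Blood pressure: "Lowest values of mean arterial blood pressure" at randomization. Systolic pressure is not listed.
- Lactate: highest value around randomization and highest value on the 24-hour form, neither tied to a bolus.
- Mottling score and urine output: not listed.

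**Step 5. Does the sample size depend on this?** Section 6.1 assumes a difference of 1 L, SD 1.7 L, two-sided alpha 5% and power 90%. The normal approximation gives n = 2 × (1.960 + 1.282)² × 1.7² / 1² = 60.7, so 61 per arm. The two-sample t-test gives 61.7, so 62 per arm and 124 in total, with power 90.1%. The stated 124 reproduces, and no trigger enters the calculation.

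**The case against.** The strongest reply is that the list is the operative text and the other paragraph only explains where the trigger came from. The list also pairs the number with a visible bedside sign, mottling beyond the kneecap, which staff may use without scoring. That narrows the practical ambiguity, and a reader with the figure can see how the sign maps to the score. It does not remove the conflict: the rationale also states what the trigger is, with a different number, and nothing in the text says which paragraph prevails.

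Four stronger readings are tempting, and the document does not support them.

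- **That the deciding values are never recorded.** Section 7.1.2 calls the list a brief overview and reserves details for a data dictionary that is not shown; section 7.1 says vital signs are taken from the medical record. The list is visibly abbreviated: section 7.1.6 wants the worst 24-hour SOFA score but does not name the Glasgow Coma Scale or arterial pressure that Appendix 2 needs. What can be said is that these values are not among the listed variables.
- **That a violation rests on the unblinded clinician's word alone.** Trained research staff enter data from chart and record, there is central and GCP monitoring, and section 7.4 gives the GCP unit direct access to records. This helps most for systolic pressure. Mottling can be checked only if someone charted it, and record access cannot decide which cut-off applies. A bias towards good adherence is possible but not shown.
- **That two triggers conflict in a way that matters.** Only mottling does; the oliguria difference is one of notation.
- **That the primary outcome is compromised.** It is measured crystalloid volume in the intention-to-treat population, adjusted for site, and needs no classification of violations. Sites using different cut-offs is an assumption, and section 3.5.2 plans training.

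**Conclusion.** The inconsistency is real and is an error in the text as written: section 3.3.1 gives the mottling trigger two incompatible cut-offs, and through section 3.3.5 the number of patients with major violations depends on which is used. The size is 1.6 percentage points of the restrictive arm per affected patient. The number affected is unknown, and it is limited to patients who actually received a bolus at score exactly 2 with no other permitted reason. The oliguria wording should be harmonised at the same time but carries almost no weight.

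The checking gap is a lesser point and conditional: it holds for the variables the protocol lists and falls away if the data dictionary already captures the triggering values.

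This should be fixed. It affects a secondary feasibility outcome and which boluses are permitted, not the sample size or how the primary outcome is measured. The document does not settle which cut-off is meant, and this review takes no position on it.

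**What to change.** 1. The sponsor should reconcile the list and the rationale paragraph in section 3.3.1 so that mottling and oliguria each have one cut-off, and check that the mottling number, the anatomical description and the figure agree. The same wording should go on the bedside chart and be the reference for the violation table in section 3.3.5.
2. Confirm that the data dictionary holds the triggering value for each bolus (systolic pressure, lactate, mottling score, or urine volume with the hours it covers). If it does not, add one field beside the indication on the bedside chart, so that major violations can be checked against the value.

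The first change costs a wording correction. The second costs one extra entry per bolus on a form the team already completes, which means slightly more bedside writing. It is a complement to the correction, not a condition for it.
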